## Abstract

**Background:**

Comprehensive geriatric assessment has been shown to improve patient outcomes, but the geriatricians who deliver it are in short-supply. A web-based method of comprehensive geriatric assessment has been developed with the potential to improve access to specialist geriatric expertise. The current study aims to test the reliability and safety of comprehensive geriatric assessment performed "online" in making geriatric triage decisions. It will also explore the accuracy of the procedure in identifying common geriatric syndromes, and its cost relative to conventional "live" consultations.

**Methods/Design:**

The study population will consist of 270 acutely hospitalized patients referred for geriatric consultation at three sites. Paired assessments (live and online) will be conducted by independent, blinded geriatricians and the level of agreement examined. This will be compared with the level of agreement between two independent, blinded geriatricians each consulting with the patient in person (i.e. "live"). Agreement between the triage decision from live-live assessments and between the triage decision from live-online assessments will be calculated using kappa statistics. Agreement between the online and live detection of common geriatric syndromes will also be assessed using kappa statistics. Resource use data will be collected for online and live-live assessments to allow comparison between the two procedures.

**Discussion:**

If the online approach is found to be less precise than live assessment, further analysis will seek to identify patient subgroups where disagreement is more likely. This may enable a protocol to be developed that avoids unsafe clinical decisions at a distance.

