### Data analysis

Agreement between the triage decisions from live-online assessments will be calculated using percentage agreement and kappa statistics, reported with 95% confidence intervals. This will also be calculated for the triage decisions from live-live assessments. Comparison of the difference in levels of agreement between the live-online group and the live-live group will be the primary measure of the reliability of the online assessment and is the basis for the sample size calculation for this project. Online assessment will be taken to be non-inferior to live assessment if percentage agreement in the live-online group is not more than 15% less than the percentage agreement in the live-live group.

The online assessment can be regarded in a similar manner to a diagnostic test, where the interest is in the number of patients recommended for a higher level of care from the online assessment compared with live assessment (i.e. false positives, specificity), and in the number of patients where important clinical diagnoses are missed in an online assessment (i.e. false negatives, sensitivity).

These measures will therefore be calculated and reported. Exploratory analyses of patient characteristics will be undertaken to examine these cases where differences of triage decision are identified. Agreement between the online and live detection of common geriatric syndromes will also be assessed using kappa statistics.

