### Sample size and power analysis

The outcome of interest will be the difference in percentage agreement between paired assessments for live-live arm and online-live arm for the question: "is residential care recommended?", scored as "yes" (1) or "no" (2). A non-inferiority study tests whether the percentage agreement between clinicians in an intervention arm (online-live) does not lie beyond the lower limit of an acceptable range (a one-tailed area of clinical indifference) when compared with the standard clinical practice arm (live- live).

The sample size of 288 subjects (114 online-live, 114 live-live) was identified to provide the study with power exceeding 80% to detect a non-inferiority margin of 15% for levels of agreement between online-live when compared with live-live arms for the decision "yes, residential care is recommended". This is based on an assumption of inter-geriatrician agreement of 60% for geriatric triage decisions [8], allowing a two-sided type 1 error rate of 5%. With a 15% allowance for attrition, the adjusted sample size is 268 (i.e. 228/(1-0.15)). After rounding, 270 cases will be required in total between all sites.

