## Discussion

This study is designed to identify the strengths and weaknesses of an online method of CGA. It seeks to identify whether consistent, reliable and safe recommendations can be made online. Even if the online decisions prove to be deficient to some extent, the study will allow effectiveness to be weighed against cost and may develop a methodology to identify patients who can be safely assessed online as opposed to those who require in-person consultation. A clinical algorithm would then enable online clinical reviewers to quickly determine whether a case requires live assessment. If successful, online CGA has the potential to increase access to geriatrician expertise, especially in rural and remote locations or areas of urban isolation such as residential care.

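### The subgroup search is conditional in the abstract but unconditional in the Methods, and the Methods wording centres on discordant cases, which alone cannot show where disagreement is more likely

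*Protocol article*

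**What the plan says.** Three places in the protocol article describe the work on patient characteristics.

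- **Abstract, Discussion:** "If the online approach is found to be less precise than live assessment, further analysis will seek to identify patient subgroups" in which disagreement is more likely. The hope is that this will lead to a protocol that avoids unsafe decisions at a distance.
- **Data analysis:** "Exploratory analyses of patient characteristics will be undertaken to examine these cases where differences of triage decision are identified". No condition is attached, and the cases named are those with differing decisions.
- **Discussion:** "Even if the online decisions prove to be deficient to some extent, the study will allow effectiveness to be weighed against cost", and the study "may develop a methodology to identify patients who can be safely assessed online as opposed to those who require in-person consultation". A clinical algorithm for online reviewers is foreseen.

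The primary criterion, in Data analysis, uses overall agreement: online is non-inferior if live-online agreement is "not more than 15% less than the percentage agreement in the live-live group". The abstract's condition refers neither to this margin nor to any other threshold. Study design states that the comparison with live-live pairs is there to tell disagreement caused by the online format apart from ordinary differences between geriatricians.

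**The concern.** A reader cannot tell whether the work on characteristics is always done or follows only a deficit, nor what would count as a deficit. *Less precise* could mean any lower observed agreement, a statistically significant reduction, or failure to meet the 15-point margin. These differ, and online could be non-inferior yet still agree less often.

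The second problem is one of method. Where disagreement is more likely is a question about rates. A description of the discordant online-live cases supplies numerators only. It also sets aside the live-live arm, which the design includes precisely to measure background disagreement.

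At stake is the longer-term product: a way of telling which patients can be assessed online. A characteristic could be labelled a warning sign merely because it is common, or because geriatricians disagree about such patients even when both see them in person.

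**Working it through.** **Inputs**

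- Arm size: 114 online-live and 114 live-live (Sample size and power analysis). The printed total of 288 does not match 114 + 114 = 228. The attrition step uses 228: 228/0.85 = 268.2, given as 268.
- Agreement: 60%, from the "assumption of inter-geriatrician agreement of 60% for geriatric triage decisions" in the same section.
- Subgroup sizes and deficits: not given. Those below are assumptions, shown as a range.

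The arm size of 114 does not reproduce from the stated inputs. With 2 × 0.6 × 0.4 × (z_α + z_β)²/0.15², the result is 168 per arm at one-sided 0.025 and 132 at one-sided 0.05, for 80% power. That is a separate issue. I use 114 as printed, and the argument does not depend on it.

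**1. Background disagreement**

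Expected discordant online-live pairs with no online effect: 114 × (1 − 0.60) = 45.6, about 46. The live-live arm has the same expectation. If agreement on the yes/no residential care question were 80%, the figure would be 114 × 0.20 = 22.8, about 23.

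**2. How many discordant pairs an online effect would add**

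Extra pairs = 114 × (subgroup share) × (loss of agreement in that subgroup), with no loss elsewhere.

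| Assumed share | Assumed loss | Extra discordant pairs | Total discordant | Extra as share of total |
|---|---|---|---|---|
| 10% | 30 points | 3.4 | 49.0 | 7% |
| 20% | 25 points | 5.7 | 51.3 | 11% |
| 20% | 30 points | 6.8 | 52.4 | 13% |

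In these scenarios some 87% to 93% of the discordant online-live cases are of the ordinary kind.

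**3. Why the denominator and the other arm are needed**

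Take the middle row. The subgroup has 0.20 × 114 = 22.8 online-live pairs, of which 65% disagree: 14.8. The other 91.2 pairs disagree at 40%: 36.5. The subgroup therefore makes up 14.8/51.3 = 29% of the discordant cases. At least three situations give that same 29%:

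- 20% of patients have the characteristic, with 65% disagreement online and 40% live-live (a real online effect);
- 29% of patients have it, with 40% disagreement everywhere (no effect of any kind);
- 20% of patients have it, with 65% disagreement in both arms (hard cases, but no online effect).

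The concordant pairs rule out the second. The live-live arm rules out the third.

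**4. Precision of the better analysis**

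Taking 60% agreement in both arms, the 95% half-width for the arm difference within a subgroup of n per arm is 1.96 × √(0.48/n). For the arm-by-characteristic contrast it is 1.96 × √(0.48/n + 0.48/(114 − n)).

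| Subgroup share | n per arm | Arm difference in subgroup | Arm-by-characteristic contrast |
|---|---|---|---|
| 20% | 22.8 | ±28 points | ±32 points |
| 10% | 11.4 | ±40 points | ±42 points |

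Only very large differences would stand out, so the result is descriptive.

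**The case against.** The tempting stronger reading is that the subgroup search happens only after an overall deficit, so that a non-inferior result would leave an unsafe subgroup unexamined. The document does not support this. Data analysis is the operative text, and it plans the exploratory work whatever the primary result. The same section commits, also unconditionally, to reporting over-recommendation of higher care and missed important diagnoses as specificity and sensitivity measures. Nor can one calculate how often the abstract's condition would be met, since that requires equating *less precise* with missing the margin, an equation the document never makes.

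Three further objections have some force.

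- Nothing says that concordant pairs will be excluded. The abstract's own aim implies rates, and Data collection does not limit the interRAI AC data to discordant cases. So the fault lies in what the Data analysis sentence commits to; a decision to discard data is not shown.
- Because arms are randomised, comparing the mix of characteristics among discordant cases between arms would carry some relative information about an online effect. The sentence plans no such comparison, and it would not give differences in percentage agreement, the scale of the primary criterion.
- Choice of model and list of characteristics commonly belong in a full protocol or SAP not shown here, and the aims are hedged. That is why missing detail is not counted. The mismatch between two printed statements, and the framing around discordant cases, stand in the article itself.

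**Conclusion.** The point holds as an inconsistency plus a poorly framed exploratory analysis. The conflict between abstract and Methods, and the undefined trigger, are matters of text and need no assumption. The methodological part is general, and its size follows from the protocol's own 60% and 114: about 46 ordinary disagreements expected among the online-live pairs, against which an online effect confined to a minority would add only a few (3 to 7 in the assumed scenarios). The 46 depends on the 60% applying to the yes/no question; at 80% it would be 23, with the same logic.

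The primary comparison is unaffected. This is a worthwhile, inexpensive improvement and not a threat to the trial's main conclusion.

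**What to change.** 1. In the abstract's Discussion, remove the condition, so that it agrees with Data analysis.
2. In Data analysis, replace the sentence on exploratory analyses with wording such as: *Whatever the primary result, agreement on the triage decision (yes/no) will be compared by a short list of interRAI AC characteristics named in advance, using all pairs in both arms and an arm-by-characteristic term. Results will be given as differences in agreement with 95% confidence intervals and are exploratory.* Cognition, communication and activities of daily living, which the Background lists among the instrument's scales, are natural candidates. A descriptive review of discordant cases can remain as a supplement.

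**Cost:** two sentences and a small amount of analysis. The interRAI AC data are already to be collected, and neither patient care nor the primary outcome changes. The drawback is the imprecision shown above, so the list should be short. A wide interval should be read neither as evidence that a subgroup is safe nor as evidence that it is not.

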**Trial registration:**

Trial registration number: ACTRN12611000936921

## Background

Comprehensive geriatric assessment (CGA) is a core procedure in specialist geriatric care. There is evidence that this process improves functional recovery, reduces morbidity and attenuates demand for long term institutional care [1]. It is central to hospital triaging processes which direct patients to formal inpatient geriatric assessment, rehabilitation, long term institutional care and complex community support programs. Geriatric consultation services are the vehicle for delivering CGA to older hospitalised patients who are not located in specialist geriatric units.

Geriatric consultation is delivered by geriatricians, gerontic nurses - alone or in partnership - sometimes with support from other allied health specialists. The availability of these aged care specialists, and the specialist services within which they work, is currently inadequate. Furthermore, the undersupply is mal-distributed, with access considerably worse in provincial cities and rural communities [2].

An innovative web based model of comprehensive geriatric assessment has been developed by The Centre for Research in Geriatric Medicine (CRGM) at the University of Queensland (UQ)[3,4]. This system utilises the interRAI Acute Care (AC) instrument, a validated assessment tool developed by the interRAI international collaborative to support evaluation of older people in acute hospital settings [5]. The interRAI AC comprises 121 individual clinical items that profile the pre-morbid and current status of the patient. The individual items have been shown to be clinically relevant and to have overall "substantial" levels of inter-rater reliability [6]. The interRAI AC incorporates screeners for common geriatric syndromes, risk assessment tools for adverse outcomes and a range of scalar measures that enable assessment of severity or dependency in the domains of pain, cognition, communication, and activities of daily living. It also includes algorithms to identify patients most likely to benefit from preventive or curative interventions, along with guidelines for further management. The instrument is administered by trained nurses who collect standardised patient data, and enter it onto a web based database. This data is then used by the geriatrician to facilitate patient assessment and provide recommendations either "online" or in conjunction with an in-person consultation. The system has also been used to support case preparation for distance assessment using video-conferencing [7].

### Research aims

This study aims to determine whether appropriate and reliable geriatric triage decisions can be made using CGA performed "online", by establishing whether agreement between "online" and "live" triage decisions is comparable (i.e. non-inferior) to inter-rater agreement for conventional "live" geriatrician assessment. It will also explore the accuracy of the procedure in identifying common geriatric syndromes, and its cost relative to conventional "live" consultations.

The key research question is: What is the level of agreement in triage decisions made by clinicians "online" and "live"?

Subsidiary research questions will provide further insight into reliability, safety and cost effectiveness:

• Is the number of patients recommended for a higher level of care (than their prior living arrangement) greater for "online" consultations?

• How often are "important" clinical diagnoses detected during live consultation that are not identified "online"?

• What is the level of agreement in detection of the common geriatric syndromes (delirium, dementia, depression) "online" compared to "live" consultation?

• What are the costs of "live" and "online" assessment procedures?

• What is the relationship between cost and effectiveness?

## Methods/Design

### Setting and participants

The study will be conducted at 3 large Australian hospitals: Princess Alexandra Hospital, Brisbane, Queensland; Box Hill Hospital, Box Hill, Victoria; and The Northern Hospital, Melbourne, Victoria. As the study is designed to evaluate the performance of the online approach when delivered by professionals with experience in using the interRAI AC instrument, at Box Hill Hospital and The Northern Hospital, where the nurses and geriatricians are new to the approach, there will be a "run in" series of 25 cases per geriatrician. This study has been approved by the Human Research Ethics Committee at each site and UQ.

All acutely hospitalised patients referred to the geriatric consultation service at each site will be considered for inclusion in the study. Patients who have previously been consented and reviewed for the study (in a former hospital episode) and those who are already known to one of the study geriatricians will be excluded.

Consent for participation in the study will be secured by the nurse administering the interRAI AC instument prior to the commencement of the consultation. Non-consenting patients will receive the "normal" geriatric consultation for the hospital site. Full demographic and limited clinical information will be secured for non-consenting subjects to enable examination of potential bias. We anticipate consent rates in excess of 95% based on previous research experience with similar subjects, and on the experience of a previous pilot study [8].

### Study design

The design aims to measure the level of agreement in triage decisions made "online" with those made for the same patient at "live" assessment, and to compare this with the level of agreement between two independent geriatricians each assessing a patient at a live consultation. The aim is to distinguish decision disagreement attributable to the online format of assessment from the 'usual' inter-geriatrician differences in clinical decision making. It is beyond the scope of this study to establish the "online-online" inter-rater reliability; this will be examined in a subsequent study and reported separately.

Each consenting patient will undergo sequential assessment by two independent geriatricians, designated "geriatrician 1" (G1) and "geriatrician 2" (G2), in one of the following randomly allocated configurations: live-live (G1-G2), live-live (G2-G1), online-live (G1-G2) or online-live (G2-G1). The patient recruitment and randomisation process is outlined in Figure 1.

**Figure 1 F1:**
[figure not shown]
**Procedure for patient recruitment and allocation to paired consultation method**.

The paired geriatricians will be blinded to the results of their colleague's assessment. In the case of live-live assessments the order in which the geriatricians consult the patient will be randomly allocated in order to minimise any systematic influence that the interaction of the first geriatrician with the patient may have on the second assessment.

In all cases, the interRAI AC instrument will be administered by a trained nurse. Once these findings have been entered by the nurse into the software system, a geriatrician consultation will follow. Paired geriatrician assessments will be completed in the time it usually takes for a geriatrician assessment to occur following referral to the geriatrician consultation service at that site.

For live assessments, the assessing geriatrician will have access to the interRAI AC instrument data online. The geriatrician will also be able to read the medical record. The nurse will not interact directly with the geriatrician, in order to reduce the risk of contamination of decisions when consecutive live assessments are made.

For online assessments, the geriatrician will have access to the interRAI AC instrument data online only. The geriatrician will conduct the assessment without direct contact with the nurse. The geriatrician will not have access to the medical record. However, any online test results (e.g. radiology and pathology) which are usually accessed electronically will be available to both doctors, replicating the process that would occur in a distance assessment.

### Data collection

The CGA software will collect patient level data and provide a web report for online assessors to view. At the conclusion of the assessment, the geriatricians will record geriatric triage decisions on a standard research form. Other data, such as randomisation and timing for assessments, will be collected on printed forms and entered into an appropriate database. The following data will be collected:

▪ InterRAI AC data (demographic and clinical information), collected by the nurse administering the interRAI AC instrument.

▪ Geriatrician recommendations for discharge destination: direct discharge to the community; transfer to inpatient rehabilitation or a geriatric unit; transfer to permanent residential care, including a distinction between the need for a high or low level of care (equivalent approximately to Skilled Nursing Facilities or Assisted Living in the North American context).

▪ Geriatrician prediction of discharge destination and location in 3 months: own home; residential care (high or low) or "likely to be deceased". This will provide an estimate of the ability to prognosticate using online assessment, as compared with live consultation.

▪ Presence of geriatric syndromes detected by the geriatrician (including delirium, dementia and depression).

▪ Diagnoses made by the geriatrician during assessment which were not recorded in the online report. These will be classified into those already documented in the medical record and those newly identified by the geriatrician.

▪ Costing data. Direct and indirect time contributions by relevant personnel will be recorded using time sheets. Estimates of software related costs will be calculated from data obtained from the UQ Centre for Online Health. This will be supplemented by costing information derived from existing working systems in Queensland.

▪ Three month follow up data. A research assistant will follow up each patient at three months to identify actual discharge destination and outcomes (location) at 3 months. This will be compared with the geriatrician's predictions.

